### Safety, ethics and dissemination

Ethics approval has been filed with the New Zealand National Health and Disability Ethics Committee. The CURE RCT clinical protocol and data usage has been filed with the New Zealand South Regional Ethics Committee (reference number 14/STH/132). The CURE trial is also registered in the Australian New Zealand Clinical Trial Registry (ACTRN12614001069640).

All results and any subsequent analysis will be published and only the participating investigators will be authors. Currently there is no plan to share data with other organisations. The data collected in this study will also be used for future research.

### Adverse event (AE) and SAE reporting

(AEs are defined as any unexpected change in physiology in a study participant associated with either the RM_max_ or PUMP. This does not necessarily have to have a causal relationship with the aforementioned procedures. Typically, this would be an unexpected, non-life-threatening event, which rapidly resolves following simple corrective measures. For example, hypotension will occur in most participants undergoing an RMmax or PUMP. However, if the procedure had to be shortened or abandoned, but the participant recovered with simple corrective measures (e.g. temporarily increasing noradrenaline by ≥ 5 mcg/min) or giving > 500 ml fluid bolus) this would be recorded as an AE. It is very important these events are accurately recorded as risk factors for AEs that need to be defined when carrying out RMs (as seen in Additional file 3).

SAEs are defined as any untoward medical occurrence that (1) results in death; (2) is life-threatening; (3) prolongs hospitalisation or (4) results in disability or incapability. However, baseline mortality in the patients in intensive care who are enrolled in the trial will likely be high due to the critical illness necessitating admission to the ICU. Despite attempts at prevention, trial participants will frequently develop life-threatening organ failure(s) unrelated to study interventions. Events that are a part of the natural history of the primary disease process or expected complications of critical illness will not be reported as SAEs in this trial. Additionally, events already defined and reported as study outcomes, such as mortality or re-admission to the ICU, will not be labelled and reported separately as SAEs unless they are considered to be causally related to the study intervention or are otherwise of concern in the investigator’s judgement.

SAEs will be reported to the principal investigator within 24 h of any investigator becoming aware of the event. The minimum information to report includes:
Patient trial identifierThe nature of the eventThe time the event commenced and ceasedAn investigator’s opinion of the relationship between study involvement and the event (not related, unlikely, possibly, probably or definitely related)Whether treatment was required for the event and what treatment was administered

SAEs could include pneumothorax, hypotension leading to cardiac arrest, transient desaturation leading to severe or prolonged desaturation, tachycardia, bradycardia, arrhythmia, anaphylaxis and unintended protocol deviations.

In the unlikely event of a physical injury to the participant as a result of their participation in this study, they will be eligible to apply for compensation from the Accident Compensation Corporation (ACC) NZ within its limitations. If the participant’s family/friend have any questions about the ACC, they will be able to ask the researchers for more information before they agree to take part in this trial.

ACC cover is not automatic and their case will need to be assessed by the ACC according to the provisions of the 2001 Injury Prevention Rehabilitation and Compensation Act. If the claim is accepted by the ACC, the patient still might not receive compensation. This depends on a number of factors such as whether they are earners or non-earners. The ACC usually provides only partial reimbursement of costs and expenses and there may be no lump sum compensation payable. There is no cover for mental injury unless it is a result of physical injury. If your relative or friend has ACC cover, generally this will affect their right to sue the investigators.

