#### Adherence to the intervention

Patients recruited into this study will be under constant supervision in the ICU. However, their outcomes will be measured based on the intention-to-treat principle, taking into account protocol variations, which naturally occur. These variations will be reported to the primary investigator at the earliest opportunity and followed up. There will be detailed training on the use of CURE equipment and on the protocol, to allow adherence to trial.

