## Recruitment manoeuvres (RM)

Patients enrolled in this study will undergo RMs. The RMs are only carried out by senior medical staff or senior trainees familiar with this technique. RM_Max_ and PUMPs are for participants randomised to the MBV protocol arm only. Patients assigned to the SPV arm may undergo a staircase RM (SRM) at the discretion of the treating clinician according to standard practice. (see “Standard practice staircase recruitment manoeuvre”).

All RMs will be performed in SIMV pressure controlled (PC) ventilation mode. The peak inspiratory pressure (Pi) is set to achieve a V_T_ of 6–8 ml/kg IBW. Preferably, V_T_ should result in DP ≤ 15 cmH_2_O above PEEP.

Before and after each RM, ABGs (pH, PaCO_2_, PaO_2_, HCO_3_), SpO_2_, end-tidal CO_2_ partial pressure (ETCO_2_), FiO_2_, PEEP, RR), and V_T_ will be recorded. In addition, during the RM_max_ (model-based ventilation arm) or (standard practice ventilation (SRM) arm, at each PEEP increment, Heart rate, rhythm, mean arterial pressure (MAP), SpO_2_, FiO_2_, V_T_, RR, ETCO_2_ and rates of use of vasoactive drugs will be recorded. This data will be valuable in assessing the safety of the RM_Max_, PUMP and SRM.

In many cases, where the lung stiffness, or respiratory elastance (E) is high, it will not be possible to deliver a V_T_ of 6 ml/kg IBW. Furthermore, during the RM, the delivered V_T_ may fall further as the elastance increases. As a result, it may be necessary to increase the respiratory rate to accommodate the reduction in minute ventilation. For example, if E is > 40 cmH_2_O/L (or compliance < 25 ml/cmH_2_O) in a patient weighing 58 kg (IBW), (normal range 15–20 cmH_2_O/L), the V_T_ will be < 6 ml/kg (< 350 ml) when the driving pressure is 15 cmH_2_O.

It is important that oxygenation targets in both arms are carefully followed to ensure a fair comparison between them. The SpO_2_ will be kept in the target range prior to any RM. This approach allows small decreases in oxygenation to be detected during the decremental PEEP phase of the recruitment manoeuvre, while also providing a sufficient buffer in the event of significant de-saturation due to ventilation perfusion (V/Q) mismatch. V/Q mismatch increases with higher airway pressures when pulmonary arterial blood is shunted away from the pulmonary capillaries by-passing aerated regions of the lung.

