### RM checklist

Before performing any RM, the following criteria are considered. Any RM must be delayed until these conditions are corrected in the consideration of the following at-risk patient conditions:
Haemodynamic instability (e.g. ongoing haemorrhage).Not optimally resuscitated with fluids (e.g. stable blood pressure, but pulse pressure variation ≥ 12% because of inadequate left ventricular preload)? This is only applicable in the absence of spontaneous breathing.Evidence of barotrauma since enrolment?
If there is new barotrauma, RMs must not be attempted and the participant will be withdrawn from trial. They will continue to be observed and followed up. A SAE will be reported.

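### Non-serious adverse events are defined only around the intervention arm's manoeuvres, so AE rates cannot be compared between arms

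*Protocol article*

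**What the plan says.** The AE definition in the section on AE and SAE reporting reads: "AEs are defined as any unexpected change in physiology in a study participant associated with either the RM_max_ or PUMP". No causal link is required. The worked example is a manoeuvre shortened or abandoned for hypotension, with recovery after a simple measure such as raising noradrenaline by at least 5 mcg/min or giving more than 500 ml of fluid.

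The section Recruitment manoeuvres (RM) allocates the procedures: "RM_Max_ and PUMPs are for participants randomised to the MBV protocol arm only". For the control arm it says: "Patients assigned to the SPV arm may undergo a staircase RM (SRM) at the discretion of the treating clinician". It requires physiological recordings around each manoeuvre and, for RM_Max and SRM, at each PEEP increment. It gives the reason: "This data will be valuable in assessing the safety of the RM_Max_, PUMP and SRM". The section RM termination applies one set of desaturation, heart-rate, arrhythmia and hypotension criteria to every manoeuvre in both arms.

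SAEs are defined without reference to arm or procedure: "SAEs are defined as any untoward medical occurrence that (1) results in death", with further seriousness criteria. That capture is then limited: "expected complications of critical illness will not be reported as SAEs in this trial". Events already counted as study outcomes are also not reported as SAEs unless judged causally related to the intervention or otherwise of concern.

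On new barotrauma found before a manoeuvre, the RM checklist says "the participant will be withdrawn from trial". It then adds that observation and follow-up continue and that an SAE is reported. Under Adherence to the intervention, the article says of all participants that "their outcomes will be measured based on the intention-to-treat principle".

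**The concern.** A between-arm comparison of adverse events needs the same event definition, applied over the same period, in both arms. Here the definition is tied to two procedures that only one arm receives. Any table of non-serious AEs by arm built on it would show events under MBV and a structural zero under SPV. That zero would carry no information about how often such events happen under usual care.

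The events affected matter. The AE section itself expects hypotension in most participants who undergo RM_Max or PUMP. Hypotension or arrhythmia that is not serious, and that resolves with simple measures, is neither a named outcome nor an AE in the control arm. The question a reader would ask is whether repeated protocolised manoeuvres cause more such events than usual care, and AE counts cannot answer it.

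A second, smaller matter is the wording on barotrauma. Withdrawal from the trial and analysis as randomised can coexist only if it is clear that withdrawal means stopping the manoeuvres, not stopping data collection or leaving the analysis set.

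**Working it through.** The protocol states no figure for this point and no power or alpha calculation applies. The check sets the sections side by side.

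1. **Which events can be AEs?** Only those associated with RM_Max or PUMP (AE and SAE reporting).
2. **Who has RM_Max or PUMP?** MBV participants only (Recruitment manoeuvres).
3. **Result of 1 and 2.** The set of SPV events that can meet the definition is empty, except where an SPV patient receives an MBV procedure by deviation. Control-arm AEs = 0 by construction, whatever the true event rate.
4. **Is the control arm free of comparable procedures?** No. The SRM is discretionary but comparable:
   - It targets a peak inspiratory pressure of 40–43 cmH2O, as RM_Max does (sections RM_Max and Standard practice SRM).
   - It shares the checklist, the cuff and alarm settings given for RM_Max, and the termination criteria.
5. **Same event, two classifications.** Take a manoeuvre stopped because MAP stays below 60 mmHg for more than 3 minutes, corrected by raising noradrenaline by 5 mcg/min:

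| Manoeuvre | Arm | Stopped under RM termination? | AE? |
|---|---|---|---|
| RM_Max | MBV | Yes | Yes |
| PUMP | MBV | Yes | Yes |
| SRM | SPV | Yes | No |

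6. **Was the omission deliberate?** The text points the other way. The recordings are meant to assess SRM safety as well. The arterial blood gas entry under Other patient information likewise names only RM_Max and PUMP, while the Recruitment manoeuvres section requires gases before and after each manoeuvre. This looks like the SRM being left out in drafting.
7. **Would adding the SRM be enough?** Not for a comparison. PUMP is scheduled twice daily for up to 10 days: 2 × 10 = 20 scheduled procedures at most, plus RM_Max. Fewer occur when the PUMP stopping conditions are met or the checklist delays a manoeuvre, and extra PUMPs are allowed for new desaturation. An SPV patient may have no SRM at all. Procedure-linked counts would still differ because opportunity differs, so a common list over a common period is also needed.
8. **What is still captured in both arms?**
   - SAEs, with all reports sent to the DMC.
   - Mortality, with a stopping rule at 50, 75, 100, 125 and 160 patients per arm.
   - Desaturation events and rescue therapies, as secondary outcomes.
   - Desaturation on turning, recorded as an SAE.
   - SpO2, blood pressure and heart-rate waveforms, listed under Other patient information without restriction by arm.

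   None of these is forced to zero in SPV.

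**The case against.** The strongest reply is that the trial does not rely on non-serious AEs for its safety comparison. The routes in step 8 cover death, serious events, desaturation and rescue treatment in both arms, and the continuous waveforms would let hypotension and arrhythmia be counted later. This stands. A reader might infer from the AE definition that harm cannot be compared between arms at all; the document does not support that.

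Two limits on the reply remain. SAE capture leaves out expected complications of critical illness, and outcome events enter only on a judgement about relatedness or concern, made in a trial that cannot be double-blinded. Having waveforms is also not the same as having a stated event definition for both arms.

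It can also be said that AE recording is detailed in an additional file that is not shown. That form may cover the SRM. The printed definition does not.

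On barotrauma, a reader might infer that withdrawn patients' later data are lost and that this favours MBV. The document does not say so. Follow-up is stated to continue, and analysis is by intention to treat. Even if later blood gases were missing, the direction would be unclear: with a cumulative AUC over the ventilation period, lost readings would lower the MBV value rather than raise it. Nor is detection confined to the checklist. Pneumothorax is to be considered in dyssynchrony, during assisted breathing and before an SRM, imaging findings are collected, and pneumothorax is listed as a possible SAE.

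**Conclusion.** The point holds for non-serious AEs. As defined, they can arise only in the MBV arm, the control-arm count is zero by definition, and AE rates cannot be compared between arms. The SRM has no AE category, although the protocol intends to assess its safety and stops it on the same criteria as the other manoeuvres. This follows from the text alone and rests on no assumed event rate. It does assume that the additional file on AE recording does not widen the definition.

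The point does not extend to SAEs, mortality, desaturation or rescue therapies, all of which remain comparable, with some weakening of SAEs by the exclusions noted above.

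The barotrauma wording is a secondary matter of clarity. The checklist does not say whether primary-outcome blood gases continue after withdrawal, and it should. No size or direction of bias can be derived from the document.

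**What to change.** 1. Change the AE definition so that it covers RM_Max, PUMP or SRM.
2. In both arms, over days 0–10 from enrolment, count the same listed physiological events whether or not a manoeuvre was under way: for example SpO2 below 88%, new arrhythmia, and hypotension meeting the corrective-measure thresholds already given in the AE section. Take these from monitor and chart data already collected. Settle the desaturation threshold first, because Study design and setting uses below 88% and Study outcome uses below 90%.
3. Report procedure-linked AEs separately, with the number of procedures performed as denominator. If item 2 is not adopted, label the AE data as descriptive of the manoeuvres and not as a comparison of arms.
4. In the RM checklist, reconcile the withdrawal wording with the follow-up sentence and with intention to treat: state that these patients' blood gases and outcomes continue to be collected and are analysed as randomised. The rule on stopping manoeuvres is not touched by this.

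The cost is a change of definition, a line on the control-arm record, and slightly more recording by the research nurses. Trial status says that recruitment had not begun, so the change could be made before any data exist.

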### RM termination

RMs should be terminated if at any time during the RM any of the following changes persist for more than 3 min:
Desaturation, with SpO_2_ < 88%.New bradycardia (heart rate < 60 beats per minute) or,New tachycardia (heart > 140 beats per minute) or,New arrhythmia leading to new bradycardia (2) or new tachycardia (3) or,New hypotension (reduction in MAP by 40% or MAP < 60 mmHg).

This RM termination criteria applies to all RM procedures in both arms.

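### Adverse events are defined only around procedures that the intervention arm receives, so the same stopped manoeuvre is an AE in MBV and not in SPV

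*Protocol article*

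**What the plan says.** The section Adverse event (AE) and SAE reporting ties an AE to two named procedures: "any unexpected change in physiology in a study participant associated with either the RM_max_ or PUMP". Its worked example is hypotension, recorded as an AE "if the procedure had to be shortened or abandoned, but the participant recovered with simple corrective measures". It then gives the reason for recording: "It is very important these events are accurately recorded as risk factors for AEs that need to be defined when carrying out RMs".

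The section Recruitment manoeuvres (RM) says who receives what. In the sentence that names RM_Max and PUMP together, it states that "PUMPs are for participants randomised to the MBV protocol arm only". SPV patients may instead have an SRM at the treating clinician's discretion. Of the measurements around the manoeuvres, the section says: "This data will be valuable in assessing the safety of the RM_Max_, PUMP and SRM".

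The section RM termination lists criteria that end a manoeuvre if they persist for more than 3 minutes. One is "New hypotension (reduction in MAP by 40% or MAP < 60 mmHg". It closes with: "This RM termination criteria applies to all RM procedures in both arms".

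SAEs are defined in the AE section without reference to a procedure or an arm.

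**The concern.** The protocol applies one physiological stopping rule to every manoeuvre in both arms, but gives the resulting event a safety label in one arm only. An SPV patient treated as assigned cannot have an AE, whatever happens during an SRM. A zero in the SPV column of an AE summary would reflect the definition, not an observation.

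Two things are at stake. First, a reader of AE counts by arm could not separate the effect of the intervention from the effect of the definition. Second, the protocol says that the safety of all three manoeuvres is to be assessed, but its AE definition leaves one of them out.

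There is a related gap on the MBV side. PUMP is among the procedures whose safety is to be assessed, but mean arterial pressure (MAP) and vasoactive drug rates are listed for recording only during RM_Max and SRM.

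**Working it through.** No figure in the plan needs reproducing, and no alpha, power or sample size enters. The check sets the sections of the protocol article side by side.

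**Step 1. Are the manoeuvres alike enough for the same event to arise?** The sections RM_Max; MBV and Standard practice SRM give the same deep sedation, the same rocuronium dose (1.0–1.5 mg/kg) and the same target peak inspiratory pressure (40–43 cmH2O). Hypotension is a foreseeable complication of both.

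**Step 2. Follow one event through the rules.** Take a manoeuvre stopped because MAP stays below 60 mmHg for more than 3 minutes, with recovery after a temporary increase in noradrenaline.

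| Question | MBV (RM_Max or PUMP) | SPV (SRM) |
|---|---|---|
| Does the shared termination rule apply? | Yes | Yes |
| Is the procedure named in the AE definition? | Yes | No |
| Is the event an AE? | Yes | No |
| Is it an SAE, if it is not life-threatening, disabling or prolonging the stay? | No | No |

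The rows differ only where the AE definition enters. Hypotension is the clean case because the SAE examples name it only when it leads to cardiac arrest. Bradycardia, tachycardia and arrhythmia are listed among possible SAEs in either arm.

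**Step 3. What is the SPV count?** The definition names RM_Max and PUMP, and the protocol gives neither to SPV. The AE count for SPV patients treated as assigned is therefore 0, however many SRMs are done and however many are stopped.

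**Step 4. Would naming the SRM make raw counts comparable?** Not by itself, because exposure differs by design.
- MBV: an RM_Max at the start, PUMP twice daily until a stopping condition or day 10, extra PUMPs for suspected de-recruitment, and repeat RM_Max under set conditions.
- SPV: an SRM only by clinical judgement, considered when PEEP is at least 15 cmH2O and FiO2 at least 60% after other measures.

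MBV will have far more procedures per patient. A symmetric definition needs the number of procedures beside it.

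**Step 5. What is recorded during a PUMP?** Before and after every manoeuvre, the list covers blood gases, SpO2, end-tidal CO2, FiO2, PEEP, respiratory rate and tidal volume. The further list, "at each PEEP increment, Heart rate, rhythm, mean arterial pressure (MAP") and the rest, including vasoactive drug rates, is given for RM_Max and SRM only. Yet the AE section expects hypotension in most participants undergoing RM_Max or PUMP, and its example of a corrective measure is a noradrenaline increase of at least 5 mcg/min. The two quantities most relevant to that AE are missing from the PUMP list.

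**The case against.** The strongest reply is that no planned analysis is affected. AEs are not a primary or secondary outcome, the stopping rule uses mortality, and no between-arm AE test is described. The stated purpose of the AE log is to define risk factors when manoeuvres are carried out, and a log of the two software-guided procedures serves part of that. This stands, and it limits the point to interpretation and internal consistency.

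A second reply is that the SRM is measured: heart rate, rhythm, MAP, SpO2 and vasoactive rates are recorded at each PEEP increment, and blood pressure waveforms are collected in both arms. SAEs cover both arms and go to the data monitoring committee. This also stands. The label is missing, not the data, and what goes unlabelled is the transient, quickly reversed SRM event.

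A third reply is that Additional file 3, cited for AE recording, may cover SRMs. It is not shown, so this cannot be settled. The definition in the article is explicit, and the general reference to manoeuvres later in that paragraph does not widen it.

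On PUMP, the required arterial line, the MAP-based termination rule and the stored waveforms already supply pressure data. That weakens the case for adding MAP, but the waveform list does not include vasoactive drug rates.

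A reader might infer that any MBV excess in AEs would be an artefact, or that the plan builds in a false safety signal of calculable size. The documents do not support this. They give no AE risk and no SRM frequency. Assuming equal patient-level risk in the two arms would ignore the much greater procedure exposure in MBV, so part of any MBV excess may well be real.

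**Conclusion.** The point holds as a defect of definition. Under the written rule, SPV AEs are zero by construction, the same stopped manoeuvre is classified differently by arm, and the AE section conflicts with the stated aim of assessing SRM safety. AE counts by arm therefore cannot be compared.

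The size is categorical: every non-serious SRM complication is left out, and none of those tied to RM_Max or PUMP is. How many events that means cannot be derived, because the article gives neither an AE rate nor the share of SPV patients expected to have an SRM.

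A reader might go further and infer that SRM complications are unmeasured or that control patients are unmonitored. Neither follows, given the SRM recordings and an SAE definition that covers both arms. The primary analysis and the mortality stopping rule are untouched.

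The conclusion assumes that SPV patients receive neither RM_Max nor PUMP, as the protocol directs, and that Additional file 3 does not override the definition in the text.

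**What to change.** 1. In Adverse event (AE) and SAE reporting, define an AE as an unexpected change in physiology associated with any recruitment manoeuvre: RM_Max, PUMP or SRM. Apply the hypotension example to all three.
2. Report AEs by assigned arm and by type of manoeuvre, with the number of procedures done, and give rates per procedure as well as per patient.
3. In Recruitment manoeuvres (RM), add MAP and vasoactive drug rate to what is recorded during a PUMP.

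The cost is small: a wording change, a few more AE forms in SPV and two more items on the PUMP sheet. Under Trial status, recruitment had not begun at version 2.0, so the change could have been made before any patient was enrolled. Counting AEs outside procedures, or adding a hypotension endpoint from the waveforms, is not needed to close this gap.
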